### **9.5 [Data Safety Monitoring Board (DSMB) / Safety Committee]**

Not applicable.

## **10. STATISTICAL ANALYSIS**

### **10.1 Primary study parameter(s)**

Scar quality 12 months post-surgery assessed by the observer score of the POSAS scale will be tested for normality before univariate analyses will be performed. If the data are normally distributed, a paired student's t-test will be used for comparison of the data. Otherwise the Wilcoxon signed-rank test will be applied.

### **10.2 Secondary study parameter(s)**

All continuous data will be assessed with a paired student's t-test, or when data are not normally distributed with a Wilcoxon signed-rank test.

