## 1. INTRODUCTION AND RATIONALE

Patients with deep dermal burns or full thickness wounds always require a surgical reconstruction with skin grafts to restore the integrity of the outer skin layer. Most of the deep burn wounds are covered with split thickness skin grafts (SSG) which is the standard of care (SOC) treatment nowadays. However, in order to achieve rapid wound closure in extensively burned patients, the shortage of available donor areas for skin graft harvesting represents a significant problem. As a result, coverage of the majority of burn wounds or full-thickness skin defects unavoidably requires an expansion of the skin graft before application.

Currently there are two distinct methods for skin graft expansion. The most frequently used technique worldwide is the easy and fast meshed graft technique whereby the skin theoretically can be enlarged 1.5 to 9 times. The larger the expansion rate, the less donor skin is needed. Unfortunately, it has been demonstrated that in reality the claimed expansion ratios are never achieved with meshed grafts whereby e.g. a 1:3 expansion only results in about 60% increase in size. Therefore, even more donor skin or even larger expansion ratios are needed in order to cover all wounds in severely burned patients. Various additional problems arise due to the use of widely meshed skin grafts, both for the patient and for the surgeon. Mesh-expanded skin grafts take much longer to completely epithelialize and often result in hypertrophic scar formation and contractures. Moreover, in the long-term, a lasting “fishnet or string-vest” pattern will always be visible in meshed grafted areas. An additional technical problem is that skin grafts that are meshed with a ratio above 1:3 are fragile and very difficult to handle for the surgeon.

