#### 6.4 Summary of known and potential risks and benefits

Meshed grafts: This technique for skin expansion and grafting is most widely performed, seen it is a very user-friendly and fast procedure. However, mesh grafting also has its shortcomings. Theoretically an expansion ratio from 1:1.5 until 1:9 are possible In practice, meshed grafts do not expand as much as suggested. Expansion ratios of 1:1,5 and 1:3 turned out to give an surface area expansion of 1,36x and 1,80x respectively Moreover, an expansion ratio above 1:3 is very fragile and therefore difficult to properly cover and fixate on wounds. Besides, the 'fish-net' pattern of the meshed graft remains visible in the long-term scar. For this reason, meshed grafts do not fall within the preferred skin expansion and grafting techniques for extensive wounds with limited donorsite.

Micrografting: True expansion ratios up to 1:9 are achieved, which leads to a smaller donorsite. In comparison with meshed grafts, micrografting will not give fragility problems with a large expansion ratio. Also small graft fragment can be used, in contrast with meshed grafts were only long strips of graft can be utilized (4). Therefore is a preferable technique for especially extensive wounds (2). Graft failure due to bacterial infection is limited to failure of a few islands instead of the whole graft, because of all separate gauzes. Moreover, in our experience the scar quality of micrografts showed to be very good and might even better

than the scars of meshed grafts. Drawbacks of micrografting are mainly based on a more labour-intensive and time-consuming procedure compared with meshed grafts.

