#### 8.1.2 Secondary study parameters/endpoints (if applicable)

- Long-term scar quality 3 and 12 months after skin transplantation
  - Subjective measurement of scar quality with Patient and Observer Scar Assessment Scale (POSAS). This is based on multiple aspects of scar formation such as: vascularization, pigmentation, texture, thickness, pliability, itch and pain, and is performed by member of research team and by patient.
  - Objective measurements of scar color and pigmentation with the Mexameter or Dermaspectrometer. Skin elasticity is objectively measured with the Cutometer.
- Skin graft technique preferred by patient
  - Patient gives overall indication as to what skin graft technique he/she would prefer if he/she were to require skin grafting again: weekly during admission, and at 3 and 12 months follow up
- Donorsite size and ratio of donorsite size and actual graft size (cm^2)
  - Surface areas will be calculated with a 3D-camera (Woundworks inSight)
- Take rate of skin grafts
  - Take rate will be clinically assessed at 8 +/- 2 days and expressed as the percentage of micrografted and meshed graft take
- Healing time
  - Clinical assessment of wound healing 14 and 21 days +/- 2 post application expressed as percentage of the total wound surface area healed
  - Time to complete wound closure where complete wound closure is defined as > 95% re-epithelialization of the wound with the absence of drainage and no longer needing a substantial wound dressing
- Bacterial load
  - Wound swabs for semi-quantitative investigation
  - Semi-quantitative bacteriology in both groups
  - Percentage of patients within both groups with clinical wound infection requiring systemic antimicrobial therapy
  - 'Clinical infection' is defined as the presence of cellulitis and/or visible purulence and/or lymphangitis combined with one or more of the following: local wound pain/erythema/edema/malodor

- Pain
  - Will be evaluated in the autografted target wounds with help of a Visual Analogue Scale (VAS score) on day 2 post surgery, before and after removal of Surfasoft®/Urgotul in case of meshed skin grafts or plissees in case of micrografting, and thereafter once weekly during the hospitalization period. After hospital discharge pain will be evaluated again at the 3 and 12 months follow ups
- Number of secondary procedures
  - Re-interventions in study areas due to insufficient take or necessity of reconstructive surgery
- Mobility at 3 and 12 months

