  - If articulations of limbs are involved the Quick Dash for upper extremities and the Lower extremity functional scale for lower extremities, the range of motion will be assessed with a goniometer
- Quality of life
  - Assessed at the time of hospital discharge and at 3 and 12 months after the procedure. 3 quality of life measures, the EQ5D-5L, SF36 and DLQI will be used at different points in time: at the time of hospital discharge and 3 and 12 months post wound healing
- Health economics
  - Differences in operation time, costs of materials/equipment used and staff/personnel and impact of re-interventions and the need for reconstructive surgery will be evaluated. Using regression analysis based on the processing of the EQ5D-5L, SF36 and the DLQI we will be able to construct an economic model. The model will incorporate the short-term costs involved of both skin expansion techniques as well as the long-term costs.
- Incidence of AE and SAE
  - There are no Adverse Events (AEs) expected, relating to this study (comparison of two already practiced skin grafting techniques).
  - A Serious Adverse Event (SAE) is any untoward medical occurrence in a subject who is participating in a clinical study performed. This is defined as an event that is:
    - a) fatal
    - b) life-threatening
    - c) requires or prolongs inpatient (unexpected) hospitalization
  - These SAEs will be reported directly to the METc.
  - SAEs related to surgical treatment in general will be noted in a line-listing and will be reported yearly to the METc. These are defined as an event that results in a:
    - a) pneumonia
    - b) urinary tract infections
    - c) sepsis

- d) pulmonary embolism
- e) re-operation

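### The normality rule in 10.2, read literally, sends skewed paired costs to a Wilcoxon signed-rank test, which does not test the mean cost difference that the economic model in 8.1.2 needs

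*Protocol*

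**What the plan says.** Protocol section 10.2 consists of a single rule: "All continuous data will be assessed with a paired student's t-test, or when data are not normally distributed with a Wilcoxon signed-rank test". It names no parameter and excludes none.

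Section 8.1.2 lists health economics among the secondary parameters: "Differences in operation time, costs of materials/equipment used and staff/personnel and impact of re-interventions and the need for reconstructive surgery will be evaluated". It goes on: "Using regression analysis based on the processing of the EQ5D-5L, SF36 and the DLQI we will be able to construct an economic model", and then "The model will incorporate the short-term costs involved of both skin expansion techniques as well as the long-term costs". The same section counts secondary procedures, defined as "Re-interventions in study areas due to insufficient take or necessity of reconstructive surgery".

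On the likely direction of routine costs, section 6.4 says: "Drawbacks of micrografting are mainly based on a more labour-intensive and time-consuming procedure compared with meshed grafts". Section 1 says that mesh-expanded grafts "often result in hypertrophic scar formation and contractures", in a passage about widely meshed grafts.

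The protocol gives no unit cost, cost distribution or re-intervention rate. Sections 8.1.2 and 10.2 do not refer to each other.

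**The concern.** Technique-specific costs are continuous and can be paired within a patient, so the wording of 10.2 reaches them. Two features make the rule a poor fit.

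- **Shape.** Most pairs would differ by a modest routine amount. A few would differ by the price of a re-intervention. Such differences are very unlikely to pass a normality check, so the rule would choose the signed-rank test.
- **Target.** A cost comparison needs the arithmetic mean difference, because the mean times the number of patients is the total cost. The signed-rank test uses the sign of each difference and the rank of its size. Once an expensive event holds a top rank, making it dearer changes nothing.

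If micrografting costs slightly more in most patients and saves a large sum in a few, the test can report it as significantly dearer while its mean cost is lower. The trial would then hold a rank test and a cost model that disagree, with no statement of which one stands.

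**Working it through.** **Number of pairs.** Section 4.4 uses SD 2.4 and correlation 0.5, so the SD of the paired difference is 2.4 × √(2 × (1 − 0.5)) = 2.4. For a difference of 1, the exact paired t-test power at 63 pairs is 0.902, as stated, and 63 / 0.9 = 70. These figures reproduce, and 63 pairs are used below. The protocol has no cost figure to reproduce.

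**What the test does with a large cost.** Take one assumed data set of 63 differences (micrografting minus mesh), drawn with routine mean 300 and SD 200, in which 8 mesh sites are re-treated. The sample's routine mean is 276.2.

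- Mean difference = 276.2 − 8 × (re-intervention cost) / 63. This is +22 at a cost of 2,000, −359 at 5,000 and −2,263 at 20,000.
- The smaller rank sum is 504 in all three cases. Its null mean is 63 × 64 / 4 = 1,008 and its null SD is √(63 × 64 × 127 / 24) = 146.07. So z = (504 − 1,008) / 146.07 = −3.45 and p = 0.00056 each time, with micrografting the dearer.

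The mean moves by more than 2,000 and changes sign. The test result does not move.

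**How many events the test tolerates.** Suppose every other pair is dearer with micrografting and the mesh re-interventions take the top ranks. The 5% limit for the negative rank sum is 1,008 − 1.96 × 146.07 = 721.7. Twelve events give 52 + … + 63 = 690, still significant for micrografting dearer. Thirteen give 741, no longer significant. So up to 12 of 63 re-treated mesh sites (19%) leave that result in place at any price. With a routine excess of 1 unit, the mean already favours micrografting once 12 × cost exceeds 63, that is, above 5.25 units.

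**How often, under assumed inputs.** True mean difference = routine excess + K × (p_micro − p_mesh), where K is the re-intervention cost. For 8% v 15% and K = 20 it is 1 + 20 × (0.08 − 0.15) = −0.4. The test is two-sided at 5%. Where normality was checked, Shapiro-Wilk at 5% was assumed, since the protocol names no test. It rejected in essentially every run.

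| Routine excess (SD) | K | Re-intervention rate, micrografting v mesh | True mean difference | Significant, micrografting dearer |
|---|---|---|---|---|
| 1 (0.5) | 20 | 8% v 15% | −0.4 | about 95% |
| 1 (1) | 20 | 8% v 15% | −0.4 | about 85% |
| 1 (2) | 20 | 8% v 15% | −0.4 | about 32% |
| 1 (3) | 20 | 8% v 15% | −0.4 | about 12% |
| 1 (0.5) | 20 | 15% v 25% | −1.0 | about 65% |
| 1 (2) | 20 | 15% v 25% | −1.0 | about 10% |
| 1 (3) | 20 | 15% v 25% | −1.0 | about 3% |
| 1 (0.5) | 10 | 5% v 25% | −1.0 | about 30% |
| 300 (200) | 5,000 | 2% v 10% | −100 | 99% |
| 300 (200) | 5,000 | 5% v 15% | −200 | 88% |
| 300 (400) | 5,000 | 5% v 15% | −200 | 51% |
| 300 (200) | 5,000 | 5% v 20% | −450 | 57% |
| 300 (200) | 5,000 | 5% v 35% | −1,200 | 0.7% |

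In the rows with a routine excess of 300, K is the mean of a variable re-intervention cost. In units of the routine excess, 5,000 / 300 = 16.7, which lies within 10 to 30. A paired t-test on the mean gives the wrong-direction result in about 1% of runs in the first row and 0.5% in the 5% v 15% row with SD 200.

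**The case against.** **Section 8.1.2 already gives costs their own route.** The economic model takes in short-term and long-term costs, and nothing says that its conclusion rests on a signed-rank p-value. How costs are summarised inside the model may properly be left to a later plan. This stands: a reader might infer that the signed-rank test is the only planned handling of costs, and the protocol does not support that. But the regression in 8.1.2 is described for the quality-of-life instruments, the section does not say how the cost difference is compared, and 10.2 claims all continuous data. The point concerns a rule that is stated, not detail that is absent.

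**The protocol does not predict more surgery after mesh in this trial.** A reader might infer that it does from the remark on contractures in section 1. That remark concerns widely meshed grafts. Section 5.1 uses 1:2 and 1:3 only, section 4.3 excludes wounds over joints, and a retrospective study cited in section 6.3 found equal numbers of operations, although its micrograft patients had larger burns. So the reversal is a possibility, not a forecast.

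**The size depends on invented inputs.** This stands too. An SD of 0.5 around an excess of 1 makes about 98% of patients without a re-intervention dearer with micrografting. Wider routine variation weakens the effect sharply.

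**Absolute wording fails.** The test does not ignore re-interventions: they keep their sign and take the highest ranks. Nor are cost differences certain to be non-normal. The switch in 10.2 happens only if they are.

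**Operation time.** The argument rests on rare expensive events. It does not show a defect in applying 10.2 to the duration of the index operation.

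**Conclusion.** The point holds in limited form. Read literally, 10.2 sends non-normal paired costs to a test that does not address the mean cost difference, and that test can be significant in the opposite direction.

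The wrong-direction rate ran from over 99% down to about 10% in most of the scenarios tried, and to 3% or less at the extremes. It depends mainly on the SD of the routine difference and on the re-intervention rates. Every scenario assumes 63 pairs, a routine excess for micrografting and a lower mean cost for micrografting. None of the cost or rate inputs comes from the protocol, so the range shows what could happen and does not estimate what will.

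The consequence is minor. One component of one secondary endpoint is affected. The primary POSAS analysis and the sample size are untouched.

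**What to change.** Add one sentence to section 10.2: technique-specific costs are exempt from the normality-triggered rank test and are compared as the mean within-patient difference (micrografting minus mesh) with a 95% bootstrap confidence interval, resampling patients; this estimate feeds the economic model in section 8.1.2. Operation time need not be exempted.

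The cost is that sentence and a few lines of code. The downside is a wider interval when a few very expensive re-interventions occur, which fairly reflects how little such data say about the mean.

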### **10.3 Other study parameters**

Descriptive statistics, such as means and frequencies.

### **10.4 Interim analysis (if applicable)**

Not applicable.

## **11. ETHICAL CONSIDERATIONS**

### **11.1 Regulation statement**

This study will be conducted according to the principles of the Declaration of Helsinki (Fortaleza, October 2013) and in accordance with the Medical Research Involving Human Subjects Act (WMO) and the valid Dutch laws.

### **11.2 Recruitment and consent**

Patients will be recruited in the Dutch burn centre in Beverwijk and the Belgium burn centre in Ghent. The attending doctor will determine if patient fulfils all inclusion criteria. If so, the attending doctor will discuss the content of the study, intensity for the patients and total study time with patient or their legal representative. If patient/legal representatives is interested, the attending doctor will ask for him/her permission to receive more information about the study during an additional conversation with a member of the research team. During this additional conversation a member of the research team will hand over the patient information form and the permission form of the study. Patients/legal representatives have at least 24 hours to consider their decision. Thereafter, patients/legal representatives are asked by a member of the research team to sign the permission form (informed consent). Both researcher and patient/legal representatives have to sign the informed consent. For questions they can contact the local principal investigator or the independent physician.

### **11.3 Objection by minors or incapacitated subjects (if applicable)**

The code of conduct minors is not applicable.

### **11.4 Benefits and risks assessment, group relatedness**

Patients experience no additional risks since skin grafting according to micrografting technique and meshed skin graft technique are both standard treatments.

As the POSAS, quality of life- and mobility surveys, Cutometer and Deraspectometer are non-invasive measurements requiring limited registration time the total duration of all measurements is estimated at 60 minutes per subject. No additional risks are to be expected.

### **11.5 Compensation for injury**

The sponsor/investigator has a liability insurance which is in accordance with article 7 of the WMO.

The sponsor (also) has an insurance which is in accordance with the legal requirements in the Netherlands (Article 7 WMO). This insurance provides cover for damage to research subjects through injury or death caused by the study.

The insurance applies to the damage that becomes apparent during the study or within 4 years after the end of the study.

### **11.6 Incentives (if applicable)**

Participants participating in this study receive a full compensation of the parking costs of the two follow-up appointments at the outpatient clinic. Parking fee comes down to 1,10 euro per hour. Travel costs will not be compensated, seen study measurements are performed only during regular follow-up appointments and therefore no additional travel costs are made.

## **12. ADMINISTRATIVE ASPECTS, MONITORING AND PUBLICATION**

### **12.1 Handling and storage of data and documents**

Data will be documented in an online CRF (Castor EDC, Ciwit BV, Amsterdam, the Netherlands). Castor EDC has been audited on good clinical practice (GCP) compliance by Profess Medical Consultancy and has obtained a GCP compliance certificate. After enrolment, the patients' data will be coded by:

- A letter B (Beverwijk) or G (Ghent) for the burn centre;
- A study code: MvsM;
- Number of patients in the study;

E.g.: B-MvsM-001

The key to the codes will be available to local coordinating investigator in the Red Cross Hospital, Beverwijk. The encoded data from each centre will be exported as a CSV-file to the study folder at the secured server of the Red Cross Hospital, enabling statistical analyses in SPSS for Windows. Both teams of investigators in burncentres in Beverwijk and Ghent have access to the encoded data from both centres.

All source data, including signed informed consent forms, are stored locally on a secured server. Access to the server is limited to the local investigators, coordinating investigators, and if necessary, to the members of the medical ethics committee and the health care inspectorate (IGJ). The handling of personal data will be in compliance with the AVG/GDPR. Data will be stored for fifteen years.

The data transfers between University Hospital Ghent and the Red Cross Hospital will be covered by Data Transfer Agreements, in accordance with the AVG/GDPR.

### **12.2 Monitoring and Quality Assurance**

Monitoring will not be performed for this study.

### **12.3 Amendments**

Amendments are changes made to the research after a favourable opinion by the accredited METC has been given. All amendments will be notified to the METC that gave a favourable opinion. The start of the study will be notified to the METC.

### **12.4 Annual progress report**

The sponsor/investigator will submit a summary of the progress of the trial to the accredited METC once a year. Information will be provided on the date of inclusion of the first subject, numbers of subjects included and numbers of subjects that have completed the trial, serious adverse events/ serious adverse reactions, other problems, and amendments.

**12.5 Temporary halt and (prematurely) end of study report**

The investigator/sponsor will notify the accredited METC of the end of the study within a period of 8 weeks. The end of the study is defined as the last patient's last visit.

The sponsor will notify the METC immediately of a temporary halt of the study, including the reason of such an action. In case the study is ended prematurely, the sponsor will notify the accredited METC within 15 days, including the reasons for the premature termination. Within one year after the end of the study, the investigator/sponsor will submit a final study report with the results of the study, including any publications/abstracts of the study, to the accredited METC.

**12.6 Public disclosure and publication policy**

The funders had no role in study design, data collection and analysis, decision to publish, or preparation of the manuscript.

## 13. STRUCTURED RISK ANALYSIS

### 13.1 Potential issues of concern

Not applicable.

### 13.2 Synthesis

Patients experience no additional risks since skin grafting according to micrografting technique and meshed skin graft technique are both standard treatments.

